**Fig. 2 Fig2:**
[figure not shown]
Schematic Illustration of Fascial Closure (**a**) continuous barbed suturing, (**b**) interrupted suturing

### Implementation

In each participating institution, surgeons and operating room nurses involved in the trial will receive training through presentations and demonstration videos before the start of the study. Surgeons responsible for fascial closure via mini-laparotomy must be board-certified specialists. Prior to the initiation of the trial, they are required to perform both suturing techniques using a demonstration model, and only those who are certified as competent by the study coordinating center will be allowed to perform suturing within the trial. The trial at each center may proceed only once surgeons are trained in both techniques, nurses are trained in stitch and suture counting and measurement, and the study team has confirmed readiness. Throughout the study, unscheduled audits will be performed to monitor adherence to the protocol and to ensure quality control.

### Outcome parameters

#### Primary outcome

The primary endpoint is the incidence of IH within 18 months after surgery, primarily assessed using scheduled abdominal CT imaging performed at predefined follow-up time points in all patients, with clinical examination serving as a complementary assessment.

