## Methods/design

### Trial design

The HIBISCUS trial is designed as a prospective, multicenter, open-label RCT comparing CBS with IS.

The HIBISCUS trial is a multicenter, prospective, open-label, randomized controlled study comparing continuous barbed suturing with interrupted monofilament suturing for fascial closure of mini-laparotomy incisions (Fig. 1). The study is conducted across six participating institutions in Aichi Prefecture, Japan. Eligible adults with colorectal cancer undergoing elective laparoscopic or robot-assisted resection will be randomized in a 1:1 ratio to continuous closure using a barbed absorbable suture (STRATAFIX Symmetric PDS Plus; bite width of 5 mm and stitch spacing of 5 mm) or interrupted closure using a monofilament absorbable suture (PDS Plus; bite width of 8 mm and stitch spacing of 8 mm). This study is registered in the Japan Registry of Clinical Trials (jRCT1040250129). Registration date: November 21, 2025. Ethical approval was obtained from the Certified Review Board of Nagoya City University, and the protocol has been reviewed and approved by the institutional review boards of all participating hospitals. Patients will be recruited from six hospitals in Aichi Prefecture. The planned enrollment period is 1.5 years, followed by a 1.5-year follow-up period, resulting in a total maximum follow-up duration of 3 years. The study protocol was developed in accordance with the Standard Protocol Items: Recommendations for Interventional Trials (SPIRIT) 2013 guidelines.

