#### Secondary outcomes

Postoperative wound complicationsReoperation or readmissionPostoperative wound painFascial closure time

According to the definition proposed by the European Hernia Society (EHS), IH is defined as “any abdominal wall gap with or without a bulge in the area of a postoperative scar, perceptible or palpable by clinical examination or imaging.” [28] The EHS classification of IH will also be applied.

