### Classification of incisional hernia

IH will be categorized according to its location, size, reducibility, and symptoms. The date of hospital discharge and the occurrence of postoperative complications will be recorded.

In accordance with the Japanese Guidelines for the Treatment of Colorectal Cancer [29], patients will undergo abdominal examinations, including palpation, every three months, and abdominal CT scans will be performed every six months. The following data will be collected at predefined time points.

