### Evaluation of incisional hernia by abdominal CT

Two specialists (one radiologist and one gastrointestinal surgeon) at Nagoya City University will independently and blindly evaluate the CT images. In the event of disagreement between the two evaluators, a third specialist will adjudicate and make the final determination.

To avoid bias related to the suturing method, the evaluators will be blinded to treatment allocation, and allocation information will not be accessible to them.

IH will be assessed using the following parameters:

Presence or absence of IH (based on the EHS definition)Size of the fascial defectType of hernia contents

The assessment criteria will follow the definition proposed by the European Hernia Society (EHS), which defines hernia as “any abdominal wall gap with or without a bulge in the area of a postoperative scar, perceptible or palpable by clinical examination or imaging” [30]. The study’s calendars are shown in Table 1.

**Table 1 Tab1:** Study calendar of the HIBISCUS study

Time point	Enrollment	Allocation	Post-allocation					
			Surgery	POD 30	3 months	6 months	1 year	1.5 years
Informed consent	●							
Eligibility screen	●							
Patient background	●							
Blood test	●			●	●	●	●	●
CT	●					●	●	●
Colonoscopy							●※	
Allocation		●						
Surgery			●					
Surgical outcome			●					
Intraoperative adverse event			●					
Physical examination	●			●	●	●	●	●
Pathological findings				●				
Early complications				●				
Readmission				●	●	●	●	●
Adjuvant therapy					●	●	●	
Late complications					●	●	●	●
Survival						●	●	●
Resurrence						●	●	●

※Colonoscopy is generally performed 1 year postoperatively, but may be advanced to 6 months if complete evaluation was not possible due to preoperative bowel obstruction

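### Clinical examination can supply primary events in an open-label trial, so the blinded CT reading does not fully protect the primary result from detection bias

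*Protocol article*

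**What the plan says.** All places are in the protocol article.

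- **Primary outcome.** The definition opens: "The primary endpoint is the incidence of IH within 18 months after surgery, primarily assessed using scheduled abdominal CT imaging". The same sentence then ends by adding the second method, "with clinical examination serving as a complementary assessment". The Abstract and the Objective section say the same in substance.
- **Secondary outcomes (case definition).** The definition is met by a gap "perceptible or palpable by clinical examination or imaging". It is repeated under the CT evaluation heading.
- **Trial design.** "The HIBISCUS trial is designed as a prospective, multicenter, open-label RCT comparing CBS with IS".
- **Evaluation of incisional hernia by abdominal CT.** The reading is set out as follows: "Two specialists (one radiologist and one gastrointestinal surgeon) at Nagoya City University will independently and blindly evaluate the CT images". A third specialist decides when the two disagree. On blinding, "the evaluators will be blinded to treatment allocation, and allocation information will not be accessible to them".
- **Classification of incisional hernia; Clinical evaluation.** "patients will undergo abdominal examinations, including palpation, every three months". Outpatient visits at 1 month and then every 3 months include an assessment for IH.
- **Imaging.** CT is scheduled at 6, 12 and 18 months.

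The article does not say who performs the outpatient examination or whether that person is blinded. It does not require blinded confirmation of a hernia found clinically. It does not say how a patient counts who is positive on examination but negative on CT, or has no CT.

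**The concern.** The article blinds the CT readers expressly to avoid bias related to the suturing method, so it recognises the threat. The protection covers one of the two routes by which a patient can become a primary event. The other route is palpation at outpatient visits in an open-label trial, and these visits are more frequent than the scans.

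The expectation at those visits has a direction. The stated hypothesis is that continuous barbed suturing (CBS) lowers the IH rate, and the coordinating institution already closes this way and reports 3.5% IH at one year. If examiners who know the closure method call doubtful findings more readily in one arm, the difference goes into the primary comparison. Planned events are few, so a handful of such calls could change the conclusion.

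**Working it through.** **1. Inputs.** From Sample size calculation: 11.5% in IS, 3.9% in CBS, two-sided 5%, 80% power, 192 per group. From Statistical analysis: two-sided chi-square test. The common null rate used below is the midpoint, (11.5% + 3.9%)/2 = 7.7%. The extra share x of patients called on examination alone is not in the document. It is an assumption, shown over a range.

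**2. The plan's own figure.** n = [z₀.₉₇₅·√(2p̄(1−p̄)) + z₀.₈₀·√(p₁(1−p₁) + p₂(1−p₂))]² / (p₁−p₂)²

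= [1.960·√0.142142 + 0.8416·√0.139254]² / 0.076² = 1.0530² / 0.005776 = 191.97, so 192 per group. The stated size reproduces.

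**3. How few events decide the result.** Expected events are 0.115 × 192 ≈ 22 in IS and 0.039 × 192 ≈ 7.5 in CBS. Suppose CBS has 7 events, with no continuity correction. Then 16 IS events give chi-square 3.75, p = 0.053, and 17 give chi-square 4.44, p = 0.035. Near that boundary, one clinical-only call decides significance.

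**4. Type I error with one-sided over-calling.** Set the CBS rate to p and the IS rate to p + x. Sum the binomial probabilities of every pair of counts (192 per arm) for which the chi-square exceeds 3.84.

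| x in IS only | Patients (x × 192) | Two-sided type I error, p = 7.7% |
|---|---|---|
| 0 | 0 | 5.1% |
| 0.5 points | 1.0 | 5.4% |
| 1 point | 1.9 | 6.5% |
| 2 points | 3.8 | 10.7% |
| 3 points | 5.8 | 17.4% |
| 4 points | 7.7 | 26.3% |

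The effect depends on the base rate. At x = 2 points the same enumeration gives 14.4% for p = 3.9% and 9.1% for p = 11.5%.

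**5. Either direction at the planned rates** (normal approximation, 192 per arm). Two points of over-calling in IS only move power from 80% to 92% (13.5% v 3.9%). Two points in CBS only lower it to 49% (11.5% v 5.9%).

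**The case against.** A reader might infer that, as written, a hernia felt on palpation is a primary event whatever the blinded CT shows. The document does not say that. It ranks the methods, with CT first and examination as a complement, and it applies the case definition inside the CT evaluation. It gives no rule for discordant findings, and an article may leave such a rule to the full protocol or analysis plan. A reader might also infer that the blinded reading gives no protection. That is too strong: three blinded CTs are scheduled for every patient, so bias can enter only through clinical calls that are CT-negative or lack a CT. That examiners know the allocation is likewise an inference, from the open-label design and from blinding being described for CT readers only.

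The magnitudes are assumed. Two to four points on a base of 7.7% mean about 26% to 52% more events in one arm and none in the other. At 0.5 or 1 point the inflation is slight, and over-calling in CBS would work against the hypothesis. Finally, a strict CT-only endpoint has its own cost: a real hernia repaired before the next scan, or in a patient lost before the 6-month CT, would vanish from the count.

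All of this stands as a limit on the claim and shapes the fix. It does not remove the point. The article itself fixes an either-or definition and places examination inside the primary endpoint, while the blinding and adjudication it describes cover CT only.

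**Conclusion.** The concern holds in limited form. The primary endpoint has a second route, clinical examination, for which no blinding is described, so the blinded CT reading protects the primary result only in part. The exposure is confined to clinical-only calls.

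The size and direction of any bias cannot be known from the document. In the illustration, IS-only over-calling is close to harmless at 0.5 to 1 point (5.4% to 6.5%), doubles the type I error at 2 points (10.7%), and reaches 26.3% at 4 points. These figures rest on a common 7.7% rate, 192 evaluable patients per arm, and added calls in one arm only. The stated sample size is not in question.

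**What to change.** - Define the primary event as IH on the blinded central CT reading, with the planned third-reader adjudication, at any CT up to and including the 18-month CT.
- Count a clinically suspected hernia only if the blinded readers confirm it on a scheduled CT or on a CT already taken in routine care.
- Where no later CT exists (for example, after repair before the next scan), count it only if existing records with the allocation removed confirm it on blinded review.
- Report IH by CT or clinical examination as a supporting analysis.
- Settle the wording before any outcome data are reviewed.

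**Cost.** Rewording of the endpoint and CT-evaluation sections, plus a short procedure for masking and reviewing the records of the few clinical-only cases. No new scans or readers are needed, and 192 per group is unchanged at the stated rates. Some clinically found hernias without confirming evidence will leave the primary count and appear only in the supporting analysis.

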#### Secondary outcomes

Postoperative wound complicationsReoperation or readmissionPostoperative wound painFascial closure time

According to the definition proposed by the European Hernia Society (EHS), IH is defined as “any abdominal wall gap with or without a bulge in the area of a postoperative scar, perceptible or palpable by clinical examination or imaging.” [28] The EHS classification of IH will also be applied.

### Classification of incisional hernia

IH will be categorized according to its location, size, reducibility, and symptoms. The date of hospital discharge and the occurrence of postoperative complications will be recorded.

In accordance with the Japanese Guidelines for the Treatment of Colorectal Cancer [29], patients will undergo abdominal examinations, including palpation, every three months, and abdominal CT scans will be performed every six months. The following data will be collected at predefined time points.

#### Preoperative data

Date of birthHeight and weightMedical history (including diabetes, cardiac disease, and previous laparotomy)Preoperative radiotherapy or chemotherapyPreoperative or intraoperative administration of corticosteroids or immunosuppressive agentsHistory of previous abdominal surgeryPresence of abdominal wall herniasECOG Performance Status

#### Operative data

Clinical tumor findings (primary tumor location, clinical TNM (tumor-node-metastasis) classification (cTNM), clinical stage (cStage), bowel obstruction, perforation, or fistula)Surgical approach (laparoscopic or robot-assisted)Type of surgical procedureExtent of lymph node dissection (D2 or D3)Combined resection of other organsSL:WL ratio (continuous suture group)Number of stitches (IS group)Length of incisionFascial closure timeEstimated blood lossOperative timeConversion to open surgeryUse of prophylactic antibioticsDrain placementAdministration of thromboprophylaxisIntraoperative complications (e.g., bowel injury, bleeding)Use of epidural analgesiaBlood transfusion

#### Postoperative data

Days to first flatus or bowel movementDate of initiation of oral intakeUse of analgesics after postoperative day (POD) 5Date of dischargeReoperationPostoperative complications (classified according to the Clavien–Dindo system)Adverse events (graded according to CTCAE v5.0)

The presence or absence of adverse events will be assessed through medical interviews and physical examinations. In the event that an adverse event occurs, the following information will be recorded: the name of the event, date of onset and date of recovery, worst grade, outcome, seriousness (serious or non-serious), expectedness (expected or unexpected), details of treatment and dates of treatment, and whether rehospitalization was required.

### Outpatient follow-up

Follow-up visits will be conducted in accordance with the Japanese Guidelines for the Treatment of Colorectal Cancer [29].

#### Clinical evaluation

Outpatient visits will be scheduled at 1 month after surgery and every 3 months thereafter, including assessment for:

Incisional herniaSurgical site infectionOther wound-related complicationsOther abdominal wall hernias (non-incisional)

#### Laboratory and tumor marker tests

Tumor markers (CEA and CA19-9)Laboratory blood tests, including complete blood count (white blood cell count, lymphocyte count, hemoglobin, and platelet count), albumin, and CRP

#### Imaging

Abdominal CT scans will be performed at 6, 12, and 18 months after surgery. Imaging parameters will be standardized across all participating institutions as follows:

Slice thickness: 3 mm (5 mm permitted)Contrast enhancement: 100 s after injectionContrast dose: 600 mg/kg

### Data submission and storage

All CT images obtained at each institution will be anonymized by removing personal identifiers such as patient ID, institution name, and other identifying information. The anonymized data will then be stored on CD/DVD media and sent to the study coordinating center (Department of Gastroenterological Surgery, Nagoya City University). After evaluation, the data will be securely stored in the same manner as other study data.

### Evaluation of incisional hernia by abdominal CT

Two specialists (one radiologist and one gastrointestinal surgeon) at Nagoya City University will independently and blindly evaluate the CT images. In the event of disagreement between the two evaluators, a third specialist will adjudicate and make the final determination.

To avoid bias related to the suturing method, the evaluators will be blinded to treatment allocation, and allocation information will not be accessible to them.

IH will be assessed using the following parameters:

Presence or absence of IH (based on the EHS definition)Size of the fascial defectType of hernia contents

The assessment criteria will follow the definition proposed by the European Hernia Society (EHS), which defines hernia as “any abdominal wall gap with or without a bulge in the area of a postoperative scar, perceptible or palpable by clinical examination or imaging” [30]. The study’s calendars are shown in Table 1.

**Table 1 Tab1:** Study calendar of the HIBISCUS study

Time point	Enrollment	Allocation	Post-allocation					
			Surgery	POD 30	3 months	6 months	1 year	1.5 years
Informed consent	●							
Eligibility screen	●							
Patient background	●							
Blood test	●			●	●	●	●	●
CT	●					●	●	●
Colonoscopy							●※	
Allocation		●						
Surgery			●					
Surgical outcome			●					
Intraoperative adverse event			●					
Physical examination	●			●	●	●	●	●
Pathological findings				●				
Early complications				●				
Readmission				●	●	●	●	●
Adjuvant therapy					●	●	●	
Late complications					●	●	●	●
Survival						●	●	●
Resurrence						●	●	●

※Colonoscopy is generally performed 1 year postoperatively, but may be advanced to 6 months if complete evaluation was not possible due to preoperative bowel obstruction

### Sample size calculation

Regarding the primary endpoint of IH, previous reports in laparoscopic surgery have shown an incidence of approximately 5–13% in patients undergoing conventional IS closure [17, 19–21]. Based on these data, an incidence of 11.5% was selected as a representative estimate for the IS group in the present trial.

In contrast, Pyo et al. reported an IH rate of 1.3% at 12 months following fascial closure with a monofilament polydioxanone barbed suture (MONOFIX^®^) in a prospective single-arm trial [22]. In our institution, the 1-year postoperative incidence of IH was 3.5% among 215 consecutive cases performed between June 2022 and December 2023.

Based on these previous findings, the incidence of IH in the CBS group was hypothesized to be reduced by approximately two-thirds compared with IS, resulting in an estimated incidence of 3.9%. With a two-sided significance level of 5% and a statistical power of 80%, the required sample size calculated using a two-sided chi-square test for proportions was 192 patients per group (total 384).

Allowing for an anticipated 10% dropout rate, the final target sample size was set at 422 patients. The calculation was performed using Stata software, version 17.0 (StataCorp, College Station, TX, USA).

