**Methods:**

The HIBISCUS trial is a multicenter, prospective, open-label, randomized controlled study comparing continuous barbed suturing with interrupted monofilament suturing for fascial closure of mini-laparotomy incisions. Eligible adults with colorectal cancer undergoing elective laparoscopic or robot-assisted resection will be randomized 1:1 to continuous closure using a barbed absorbable suture (STRATAFIX Symmetric PDS Plus; bite width of 5 mm and stitch spacing of 5 mm) or interrupted closure using a monofilament absorbable suture (PDS Plus; bite width of 8 mm and stitch spacing of 8 mm). Only board-certified surgeons who complete a standardized pre-trial suturing competency assessment will be allowed to participate. The primary endpoint is the incidence of incisional hernia within 18 months after surgery, assessed mainly by scheduled abdominal CT imaging, with clinical examination as complementary. Secondary endpoints include fascial closure time, postoperative wound complications (including surgical site infection (SSI)), postoperative wound pain, and reoperation or readmission. All CT images will be independently reviewed by two blinded specialists. Based on power calculations, 422 patients will be enrolled.

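### 422 patients do not cover a 10% dropout: about 380 would remain, against the 384 that the plan requires for 80% power

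*Protocol article*

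**What the plan says.** The Sample size calculation section of the protocol article gives every input. For the interrupted-suturing group, "an incidence of 11.5% was selected as a representative estimate for the IS group in the present trial". The continuous barbed suturing group is assumed to have a rate about two-thirds lower, at 3.9%. The type I error is 5% two-sided and the power 80%. From these, "the required sample size calculated using a two-sided chi-square test for proportions was 192 patients per group (total 384". The last step reads: "Allowing for an anticipated 10% dropout rate, the final target sample size was set at 422 patients".

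The Methods paragraph of the abstract repeats the final figure: "Based on power calculations, 422 patients will be enrolled". It mentions neither the dropout rate nor the power. The Trial design section fixes the allocation: patients "will be randomized in a 1:1 ratio".

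The article does not print the formula that turns 384 into 422.

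**The concern.** An allowance for dropout should leave the required number of evaluable patients after the anticipated loss. Here it does not: taking 10% away from 422 gives fewer than 384. The three printed numbers (384 required, 10% lost, 422 enrolled) therefore disagree.

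The pattern is a familiar slip. The required number is increased by 10%, when it should be divided by the 90% expected to remain. The base figure has no spare patients to absorb the difference, because 192 per group is already the smallest whole number that meets the power target. What is at stake is the accuracy of the enrolment target and, to a small degree, the power claimed for the primary comparison.

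**Working it through.** **Inputs**, from the Sample size calculation section unless noted:

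- Control rate p1 = 0.115; experimental rate p2 = 0.039; difference 0.076; mean rate 0.077
- Two-sided 5% level, z = 1.96; 80% power, z = 0.8416
- Two-sided chi-square test, 1:1 allocation (Trial design)
- Required number 384; dropout 10%; target 422

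**Step 1: reproduce the 192 per group.** With the pooled variance under the null and no continuity correction:

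n = [1.96 × √(2 × 0.077 × 0.923) + 0.8416 × √(0.115 × 0.885 + 0.039 × 0.961)]² / 0.076²

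= [0.7389 + 0.3141]² / 0.005776 = 191.97, so 192 per group and 384 in total.

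This matches the plan exactly. The base figure is not in dispute.

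**Step 2: reproduce the 422.**

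| Route | Calculation | Result |
|---|---|---|
| Add 10% to the required number | 384 × 1.10 | 422.4, printed as 422 |
| Divide by the fraction expected to remain | 384 / 0.90 | 426.7, so 427 (428 with equal arms, 214 each) |

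Only the first route gives 422. That it was the route taken is an inference, but the next step does not depend on it.

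**Step 3: apply the plan's dropout rate to its target.**

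- Remaining patients: 422 × 0.90 = 379.8, about 380, or 190 per group.
- Shortfall: 384 − 380 = 4 patients.
- Largest dropout that 422 can absorb: 1 − 384/422 = 9.0%.
- Check on the alternative: 428 × 0.90 = 385.2, which is at least 384.

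**Step 4: power at the reduced number,** by the same formula solved for power:

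power = Φ{[√n × 0.076 − 0.7389] / √(0.115 × 0.885 + 0.039 × 0.961)}, where the denominator is 0.3732.

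| Evaluable per group | Power |
|---|---|
| 192 (plan's requirement) | 80.0% |
| 190 (422 less 10%) | 79.6% |
| 211 (all 422 with an outcome) | 83.6% |

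**The case against.** The arithmetic is hard to contest; its weight is open to argument.

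- **The effect is negligible.** The gap is about 4 patients in 384 (1.1%) and 0.4 percentage points of power, and 79.6% rounds to 80%. This stands. Exact enumeration of the binomial outcomes for the same uncorrected test even gives 81.6% at 190 per group and 82.1% at 192, so the trial may well keep 80% in practice. The plan's 192, however, comes from the approximate formula, and its target has to be judged on that basis.
- **The assumptions are rougher than the gap.** An exact two-thirds reduction from 11.5% is 3.83%, which needs 188 per group (376 in total). The remaining 380 would then suffice, with 80.4% power. The control rate is itself picked from a reported range of 5–13%. This is a fair point about proportion, but the plan states 3.9% and calculates from it, so the printed figures still disagree.
- **The primary analysis is by intention to treat.** The Statistical analysis section includes all randomised participants, and the article does not say that patients without an outcome are left out. If all 422 contributed an outcome, power would be 83.6%. This limits the claim: the shortfall arises only if dropouts do not contribute. But the allowance has no purpose unless some patients are expected not to contribute.
- **Adding 10% is common shorthand.** The formula is not printed, and 422 is correct if the allowance means only a 10% increase. The text, however, calls the 10% a dropout rate, and a rate of loss is a fraction of those enrolled.

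**Conclusion.** The concern holds as a correction to a stated figure. On the plan's own inputs, 422 enrolled patients with 10% lost leave about 380, below the 384 given as necessary for 80% power. The target covers a dropout of 9.0%, or gives 79.6% power at 10%.

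This rests on three assumptions: dropout is counted as a fraction of those enrolled, those patients contribute no outcome to the primary comparison, and the stated rates of 11.5% and 3.9% apply. The choice of test, endpoint and arms is unaffected.

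**What to change.** Make the three numbers in the Sample size calculation section agree. There are two ways:

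1. **Keep 422 and restate what it delivers.** Say that it allows for 9% dropout, or that it gives 79.6% power at 10% dropout. This is free and changes nothing in the conduct of the trial. The abstract can stay as it is, since it gives neither the dropout rate nor the power.
2. **Keep 10% dropout and 80% power, and raise the target to 428** (214 per group). This adds 428 − 422 = 6 patients and requires changes to the abstract and the trial registration.

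The first is proportionate to a difference of 0.4 percentage points. Whichever is chosen, one added sentence giving the inflation formula would let a reader reproduce the target.
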